### Patient and public involvement

The eHealth intervention was developed in collaboration with representatives from both patient groups and nurses. The representatives aided in tailoring the content and follow-up plan for both HF and CRC patients’ specific health needs post-hospital discharge. Patient representatives and nurses have participated in workshops with the research team to review and assess all information provided to participants as well as the content in the eHealth application MyDignio.

### Outcome measures

An overview of all outcome measures is presented in Table 3.

**Table 3 Tab3:** Outcomes, measurements and number of items

Outcomes	Measurements	Number of items
**Primary outcome**		
Perceived self-efficacy to self-manage HF and CRC	Self-Efficacy for Managing Chronic Disease [50]	6
**Secondary outcomes**		
Treatment burden	Patient Experience with Treatment and Self-Management Scale [51, 52]	24
HRQoL	EuroQol EQ-5D-5L questionnaire [25]	5
Collaboration with healthcare services	CollaboRATE [53, 54]	3
Support from health professionals	Constructive support from health professionals [55, 56]	12
Healthcare utilisation	Patient self-reports of number of visits to the primary healthcare service and/or the specialist healthcare service	
Readmissions at 30 and 90 days	Count of readmission from electronic medical records	
Days alive and out of the hospital [57]	Patient self-reports of number of days alive and out of hospital	
**HF sub-study outcomes**		
Self-care behaviour in HF	European Heart Failure Self-Care Behaviour Scale [58]	9
Readmissions at 30 and 90 days and 6 months	Count of readmission from electronic medical records	
Medication adherence	Medication Adherence Reasons Scale-5 [59]	5

*CRC* Colorectal cancer, *EuroQol EQ-5D-5L* EuroQoL 5-Dimension 5-Level, *HF* Heart failure, *HRQoL* Health-related quality of life

#### Primary outcome measures

The primary outcome measure for this study will be patients’ self-reports of self-efficacy to manage their HF or CRC disease as measured by the six-item questionnaire Self-Efficacy for Managing Chronic Disease developed by Lorig et al. [50]. The items ask participants to rate their confidence in doing activities across several domains common for many chronic diseases (i.e., symptom control, role function, emotional functioning and communicating with physicians). All items are scored on a 10-point scale (1 = not at all confident to 10 = confident). The total score is the mean score of the six items.

#### Secondary outcome measures

Multiple measures will be used to examine secondary outcomes. These are outlined in Table 3 and briefly described below:Treatment burden will be measured with the Norwegian Patient Experiences with Treatment and Self-Management [51, 52]. The four dimensions—medical information (seven items), monitoring health (four items), medications (seven items) and medical appointments (six items)—will be used to focus on treatment burden related to areas of non-adherence in chronic illness.HRQoL will be measured using the validated and reliable EuroQoL 5-Dimension 5-Level (EQ-5D-5L) questionnaire [25]. It includes five health dimensions: mobility, self-care, usual activities, pain/discomfort, and anxiety/depression. Patients are asked to rate their current health status with responses that range from no problem to an extreme problem. It includes the EuroQoL visual analogue scale, which is a one-item visual analogue scale where patients report on ‘your health today’ using a scale between 0 and 100.Perceived support from healthcare personnel will be measured using 12 items on constructive support [55, 56]. All items are measured on a five-point Likert scale, ranging from ‘agree strongly’ to ‘disagree strongly’.Collaboration with healthcare personnel will be measured using the validated three-item questionnaire CollaboRATE [53, 54]. The three items represent three core shared decision-making activities: explanation of the health issue, preference elicitation and preference integration [60]. Each item is scored on a 10-point anchor scale from 0 (‘No effort was made’) to 9 (‘Every effort was made’).Healthcare utilisation will be captured using patients’ self-reporting of the number of visits to the primary healthcare service (i.e., general practitioner, municipal emergency department) and/or the specialist healthcare service (i.e., outpatient clinic).Days alive and out of hospital [57] will be measured by comparing a patient’s self-report data with hospital records and subtracting the number of days spent away from home due to HF- or CRC-related hospitalisation from the first reporting in MyDignio up to six months (Post-2) [61].Numbers of readmissions within 30 and 90 days will be collected from the electronic healthcare record system in the hospital.

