#### Participants

Participants in this group will be issued an iPad with only the eHealth application MyDignio. MyDignio uses a cloud-based secure database that can be accessed without an IP address, allowing information exchange using an encrypted message exchange system. Communication via chat and video links between the patients and the nurse navigators in the hospital is supported in the application. MyDignio app is linked to monitoring devices by Bluetooth for each participant to record clinical measures (i.e., blood pressure, pulse, temperature and weight).

Participants will be asked to register clinical measurements HF and CRC daily, register symptoms daily and weekly, and register well-being daily (see Table 2 for overview) into MyDignio app, which will be monitored by nurse navigators employed at the two hospitals [41]. Participants are asked to perform the clinical measurements at approximately the same time to minimise daily variance caused by meals, fluid intake and bowel movements. They will receive a reminder in the system if they have not reported the data. Additionally, participants can communicate with the nurse navigator at any time via chat and video links through the application. Before discharge from the hospital, participants will receive training from the nurse navigators on the use of MyDignio app and the monitoring devices. Instructions and contact details for accessing technical support will be provided.

**Table 2 Tab2:** Clinical measurements, symptoms and well-being reported by participants

	**Heart failure**	**Colorectal cancer**

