### Control group: routine care

The control group will only receive routine care. Routine care refers to the standard care offered after hospital discharge. For all participants in this group, this includes written discharge information, information on how to schedule a follow-up appointment at the hospital outpatient clinic or with their general practitioner if needed, and information to contact their general practitioner or municipal emergency department if worrying symptoms occur after hospital discharge. The participants will receive pertinent disease-specific information as part of routine care for both patient groups. To support participants in this group, they will be contacted by telephone between Post-1 and Post-2 to confirm their continuous participation in the trial and to offer any additional support as required.

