### Data collection

Demographic variables collected will include sex, age, education, work, living situation, other health conditions, frequency of contact with the hospital and use of digital tools. Questionnaires will be administered electronically or postally (by participant choice) at three different times: baseline, the end of the intervention (Post-1), and 6 months after baseline (Post-2). The baseline measurements will be collected in the hospital, where Post-1 and Post-2 questionnaires will be completed by the patients at home (electronically or paper, by patient choice).

Interviews will be conducted with participants in the intervention group (*n* = 30, HF *n* = 20, CRC *n* = 10) to explore the experience with the intervention around the themes of usability and acceptability and to inform the results of the intervention effects and future implementation [42]. Participants in the intervention group will also complete the Post Study System Usability Questionnaire [65] to assess satisfaction with the usability of the MyDignio app. Additionally, participants in the HF sub-study (*n* = 12) will be invited to interview twice (Post-1 and Post-2) about their experiences on HF self-care. Interviews with the nurse navigators (*n* = 8) will be conducted in one focus group. Questions will focus on their experiences of delivering the intervention and factors influencing the implementation of the intervention in the hospital. All interview guides will be co-created with patient representatives and the project group. The interviews will be conducted at the location chosen by the patients and nurse navigators. Interviews will be audio recorded, transcribed verbatim and translated into English.

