### Statistical methods

The primary assessment of the intervention effect will be performed using a mixed-model approach to the analysis of covariance (ANCOVA) with the two post-intervention scores of self-efficacy to self-care (at Post-1 and Post-2) as the dependent variable and pre-intervention self-efficacy to self-management, measurement occasion and intervention group as independent variables. The difference in treatment effects between the time points will be determined with an interaction term between the measurement occasion and intervention group. Important predictors of self-efficacy to self-managing HF or CRC or dropout will also be included in the model, as well as the stratifying variables used in the randomisation. Random effects will be included to address dependencies between repeated measures and with dropouts. The sub-study analyses of HF self-care behaviour and medication adherence comprise the primary assessment of intervention effect using the same approach. All analyses will be conducted according to intention-to-treat principles (i.e., including all participants as randomised, disregarding adherence to the assigned treatment). The main comparison will be at the six weeks (Post-1) timepoint. The analysis of secondary continuous outcomes will be performed similarly, whereas readmissions will be analysed using Cox regression. The computer software SPSS [67] and R [68] will be used for analysis and statistical calculations.

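### Days alive and out of hospital is timed from the first MyDignio entry, which control patients cannot make, so the outcome window has no start in one arm

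*Protocol article*

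**What the plan says.** Table 3 of the protocol article lists days alive and out of hospital among the secondary outcomes for the whole trial, not among those of the HF sub-study. It gives the source as "Patient self-reports of number of days alive and out of hospital". The section Secondary outcome measures describes the derivation more fully: self-report is checked against hospital records, and the quantity removed is "days spent away from home due to HF- or CRC-related hospitalisation from the first reporting in MyDignio up to six months", with Post-2 as the end.

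On who uses the application, the section on intervention participants says "Participants in this group will be issued an iPad with only the eHealth application MyDignio". The section on the control group says "The control group will only receive routine care". The only study contact described there for controls is a telephone call between Post-1 and Post-2.

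Statistical methods commits all analyses to intention to treat, with every participant kept as randomised whatever their adherence. It sends readmissions to Cox regression and says of the remaining scale outcomes: "The analysis of secondary continuous outcomes will be performed similarly".

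**The concern.** The clock for this outcome starts at something the patient does with the intervention after randomisation. That event cannot occur in the control arm, so the rule gives half the trial no observation window. In the intervention arm the start depends on engagement. A patient who never reports has no value, and a readmission or death before the first entry is not counted.

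A between-arm comparison therefore cannot be computed from the definition as it stands. Someone will have to choose a start for controls later. If that choice is made once outcome data are visible, or if it differs in kind from the intervention-arm start, it can create or hide a difference unrelated to the effect of treatment.

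**Working it through.** **The plan's own figure.** None is stated for this outcome. The only sizing that covers both disease groups concerns self-efficacy: 240 × 0.8 = 192 completers, 96 per arm, standardised difference 0.4, two-sided 5% (the sidedness is assumed). Power is Φ(0.4 × √(96/2) − 1.96) = Φ(2.77 − 1.96) = Φ(0.81) = 79.1%, against the stated 80%. It reproduces closely and does not involve days alive and out of hospital.

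**Who has a start date under the written rule.**

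| Group | MyDignio issued? | Start of window |
|---|---|---|
| Intervention, reports at least once | Yes | Date of first entry |
| Intervention, never reports | Yes | None |
| Control | No | None |

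No other section supplies a start for the second and third rows. Baseline, Post-1 and Post-2 are questionnaire times shared by both arms, but the outcome definition uses only Post-2, as its end.

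**How many patients.** With 1:1 allocation, 240 / 2 = 120 controls have no start. The number of never-reporters is not given. If 5% to 10% of the 120 intervention patients never report (an assumption), that adds 6 to 12.

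**What an improvised repair would do.** Suppose controls are counted from discharge (day 0), intervention patients from first entry on day k, and both to day 182. The maximum attainable score is 182 for controls and 182 − k for intervention patients. The values of k are assumptions.

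| First entry, k | Maximum, intervention | Shortfall against control |
|---|---|---|
| 1 | 181 | 1 |
| 2 | 180 | 2 |
| 7 | 175 | 7 |
| 14 | 168 | 14 |

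The shortfall comes from the definition alone and runs against the intervention. Omitting readmissions or deaths before day k works the other way, so the net direction cannot be known in advance.

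**Handling of death.** The only days named for subtraction are those in hospital for HF or CRC. Taken literally with a 182-day window, a patient who dies on day 30 or day 90 without readmission scores 182 − 0 = 182. Removing days after death gives 30 or 90. If a fraction p die, spread evenly over the window, the unsubtracted time averages p × 182/2 days per patient: 4.6, 9.1 and 13.7 days for p = 5%, 10% and 15%. These mortality values are illustrative and do not come from the documents.

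**Form of the data.** The outcome is one count per patient at six months, with no pre-intervention score. The model described for the primary outcome uses two post-intervention scores and a baseline covariate. Neither feature exists here.

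**The case against.** The best defence is that the practical distortion is probably small. Intervention patients are trained before discharge, asked to report daily, reminded if they do not, and contacted 24 to 48 hours after discharge. Most first entries should fall near discharge, where the table above shows a shift of a day or two. The outcome is also one of several secondary outcomes, absent from the abstract's list and from aim 2, and 30- and 90-day readmissions come from records without reference to MyDignio. All of that stands, and it limits the severity. It does not give controls a start date. Nor is this detail that a condensed article leaves to a fuller document: the article states a start, and the start cannot exist in one arm.

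A reader might infer more than the documents support:

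- **That counting only disease-related hospital days makes the arms incomparable.** The restriction applies equally to both arms. It is a narrower outcome than the name suggests and needs cause attribution, but it does not prevent comparison.
- **That the outcome cannot register a mortality difference.** The wording "subtracting the number of days spent away from home due to HF- or CRC-related hospitalisation" names no days after death, but the outcome's name and its cited definitions may already exclude them. The rule is inexplicit, not shown to be wrong. Assuming 10% against 5% mortality gives a difference of 0.05 × 182/2 = 4.6 days that a literal formula misses, but those rates are invented and the zero follows by construction.
- **That the outcome rests on reports from patients who may have died.** Table 3 reads that way, but the fuller description already brings in hospital records.
- **That a baseline-adjusted repeated-measures model is prescribed for it.** Statistical methods speaks of continuous secondary outcomes in general and does not name this one.

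**Conclusion.** The start of the window is stated wrongly. It is undefined for about 120 controls and for any intervention patient who never reports. In the intervention arm it drops events before first entry, which is inconsistent with analysing everyone as randomised. This conclusion needs no assumed figure; it follows from reading the outcome definition against the descriptions of the two arms.

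The size of any resulting bias cannot be fixed from the documents. Under assumed delays of 1 to 14 days and a control clock starting at discharge, the attainable maximum differs by 1 to 14 days. The silence on days after death and the mismatch of sources are points of clarity to settle in the same edit. The matter should be corrected before any outcome comparison, but it is confined to one secondary outcome and leaves the primary analysis and sample size untouched.

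**What to change.** In Secondary outcome measures:

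1. Start the window at the same event in both arms, either index discharge or randomisation, and end it a fixed number of days later (for example day 182) for all randomised patients. Because randomisation takes place in hospital, say how remaining index-stay days count if randomisation is chosen, or how a death before discharge is scored if discharge is chosen.
2. State that days after death are subtracted.
3. State which hospital days count. Disease-related days may be kept; all-cause days could be reported alongside.

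In Table 3, give the same source as the text: self-report compared with hospital records.

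In Statistical methods, name this outcome and specify a single between-arm comparison of one value per patient, adjusted for the three randomisation strata, without a baseline score or repeated-measures terms.

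The cost is wording in three places. Inpatient stays are already to be taken from the hospital's electronic records for the cost-effectiveness analysis; the date of death may need to be added. No extra patients, visits or questionnaires are required.

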#### HF sub-study outcome measures

Participants with HF will participate in a sub-study that aims to explore the effects of the digital eHealth intervention on HF self-care behaviours, readmissions and medication adherence. The primary outcome of this study uses the revised European Heart Failure Self-Care Behaviour Scale, a validated questionnaire comprising nine items [58], to evaluate any changes in self-care behaviours within and between the groups. Secondary outcomes will examine the number of readmissions at 30 days, 90 days and 6 months from the electronic healthcare record system in the hospital. The validated Medication Adherence Reasons Scale-5, which consists of five items [59], will be used to measure medication adherence and non-adherence behaviours for between-group comparisons.

### Patients’ and nurse navigators’ engagement with the intervention

Engagement [62] with the eHealth intervention will be assessed and explored against self-efficacy for any observable relationship. According to the World Health Organization [63], intervention adherence is the extent to which the patient’s behaviour corresponds to the intervention assigned to them. In this RCT, adherence will refer to the dose received by the participants or the extent to which participants actively engage with, are receptive to, and/or use the materials (i.e., symptom checklists) or recommended resources (i.e., monitoring equipment) [64]. Adherence will refer to engagement, for which adherence is set at 80–100% of the dose delivered (i.e., completing both daily measurements and symptom checklists). Similarly, nurse navigators’ engagement with the digital application will also be explored and evaluated. Finally, engagement data will be used to estimate cost-effectiveness.

### Data collection

Demographic variables collected will include sex, age, education, work, living situation, other health conditions, frequency of contact with the hospital and use of digital tools. Questionnaires will be administered electronically or postally (by participant choice) at three different times: baseline, the end of the intervention (Post-1), and 6 months after baseline (Post-2). The baseline measurements will be collected in the hospital, where Post-1 and Post-2 questionnaires will be completed by the patients at home (electronically or paper, by patient choice).

Interviews will be conducted with participants in the intervention group (*n* = 30, HF *n* = 20, CRC *n* = 10) to explore the experience with the intervention around the themes of usability and acceptability and to inform the results of the intervention effects and future implementation [42]. Participants in the intervention group will also complete the Post Study System Usability Questionnaire [65] to assess satisfaction with the usability of the MyDignio app. Additionally, participants in the HF sub-study (*n* = 12) will be invited to interview twice (Post-1 and Post-2) about their experiences on HF self-care. Interviews with the nurse navigators (*n* = 8) will be conducted in one focus group. Questions will focus on their experiences of delivering the intervention and factors influencing the implementation of the intervention in the hospital. All interview guides will be co-created with patient representatives and the project group. The interviews will be conducted at the location chosen by the patients and nurse navigators. Interviews will be audio recorded, transcribed verbatim and translated into English.

### Data management

Collection of personalised data is limited and only includes personal data necessary for the trial. The Services for Sensitive Data (TSD) administered by the University of Oslo [66] will be used to retrieve, store and process data from the questionnaires and interviews. Electronic questionnaire data will be retrieved using an application that includes an integrated solution for collecting sensitive data (Nettskjema), which is linked to the TSD [66]. All data containing personal identifying information and clinical variables obtained from patient’s medical records will be stored separately on research servers at Sites A and B. Only the project manager and nurse navigators will be able to access the code list connecting personal identifying data to the individual participant.

### Statistical methods

The primary assessment of the intervention effect will be performed using a mixed-model approach to the analysis of covariance (ANCOVA) with the two post-intervention scores of self-efficacy to self-care (at Post-1 and Post-2) as the dependent variable and pre-intervention self-efficacy to self-management, measurement occasion and intervention group as independent variables. The difference in treatment effects between the time points will be determined with an interaction term between the measurement occasion and intervention group. Important predictors of self-efficacy to self-managing HF or CRC or dropout will also be included in the model, as well as the stratifying variables used in the randomisation. Random effects will be included to address dependencies between repeated measures and with dropouts. The sub-study analyses of HF self-care behaviour and medication adherence comprise the primary assessment of intervention effect using the same approach. All analyses will be conducted according to intention-to-treat principles (i.e., including all participants as randomised, disregarding adherence to the assigned treatment). The main comparison will be at the six weeks (Post-1) timepoint. The analysis of secondary continuous outcomes will be performed similarly, whereas readmissions will be analysed using Cox regression. The computer software SPSS [67] and R [68] will be used for analysis and statistical calculations.

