Research on how eHealth can best support patients with HF and CRC during the period after hospital discharge is sparse [36, 38]. Therefore, a nurse-assisted eHealth intervention eHealth@Hospital-2-Home was developed and tested based on a body of research in HF and CRC patients [15, 35, 39, 40]. Existing software and application technology—the Dignio Connected Care [41]—was selected as the platform for the intervention. The eHealth intervention includes:monitoring of vital signs using connected technology (heart rate, blood pressure, pulse oximetry, temperature, weight)patient self-reporting of symptoms, health and well-beingsecure messaging between patients and hospital-based nurse navigators when patients’ vital signs exceed the acceptable rangeaccess to HF and CRC health-related educational information.

This paper presents the protocol for a randomised controlled trial (RCT) evaluating a complex intervention [42] to study the effects of the eHealth@Hospital-2-Home intervention on the primary outcome of self-efficacy in self-care in HF and CRC patients. The protocol was informed by the preliminary results from a feasibility study with the two patient groups [43] and follows the recommendations for protocol items for a clinical trial (SPIRIT) checklist [44] and the CONSORT checklist for reporting items of a randomised trial [45].

The aims of the RCT are as follows.

Primary aims:1) To evaluate the immediate (Post-1: 6 weeks) and extended effects (Post-2: 6 months) of an eHealth intervention after hospital discharge to improve patients’ self-efficacy to self-manage chronic illness. We hypothesise that participants in the intervention group will report higher levels of self-efficacy at six weeks after hospital discharge and at six months after baseline compared with the control group.

Secondary aims:2) To investigate the effects of the intervention on the secondary outcomes of the burden of treatment, HRQoL, perceived collaboration and social support from healthcare personnel, healthcare utilisation and 30- and 90-day readmission rates in the two patient groups.3) HF sub-study: To investigate the effects of the intervention on self-care behaviour, medication compliance and 6- and 12-month readmissions in participants with HF only. We hypothesise that the HF intervention group will report higher levels of self-care behaviours, better medication compliance and reduced 6- and 12-month hospital readmissions compared with the HF control group.

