### Sample size calculations

The sample size goal is 240 patients (HF = 180, CRC = 60) equally divided between the intervention and control group. Assuming a 20% dropout, a sample size of 240 will provide a power of 80% to detect, at an α error probability of < 0.05, a medium-sized standardised difference in the primary outcome (self-efficacy for managing chronic disease) of 0.4 in the disease groups combined at the first time point (Post-1). For the HF sub-study, assuming the same dropout rate of 20%, there will be 80% power to detect a standardised effect of size 0.5 for the outcome of self-reported self-care.

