### Intervention group: eHealth@Hospital-2-Home intervention

The eHealth intervention is a non-acute, alert- and communication-based service operated by nurse navigators. The intervention duration is six weeks following hospital discharge and aims to monitor and support participants.

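### Readmissions are defined as a count in fixed windows, but the only analysis named is Cox regression, which as written estimates time to first readmission instead

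*Protocol article*

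**What the plan says.** The outcome is described as a count or number wherever it is defined:

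- Table 3, for the whole trial at 30 and 90 days: "Count of readmission from electronic medical records". The HF sub-study block of the table has the same entry and adds 6 months.
- Secondary outcome measures: "Numbers of readmissions within 30 and 90 days will be collected from the electronic healthcare record system in the hospital".
- HF sub-study outcome measures: "Secondary outcomes will examine the number of readmissions at 30 days, 90 days and 6 months".

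The secondary aim in the Background uses a third term, "30- and 90-day readmission rates in the two patient groups". (The HF aim there names 6 and 12 months; that is a separate discrepancy, not pursued here.)

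For the analysis, Statistical methods gives continuous secondary outcomes the same mixed model as the primary outcome. It then says that "readmissions will be analysed using Cox regression". It does not define a time-to-first-readmission endpoint, name a recurrent-event form of Cox regression, or give a count model.

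**The concern.** A count in a window and a time to first event are different quantities. Without a recurrent-event extension, a Cox model takes each patient up to the first readmission and stops. A patient readmitted four times in 90 days contributes the same event as one readmitted once on the same day. The treatment effect is then a hazard ratio for being readmitted at all, not a ratio or difference in the number of readmissions.

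Two things are at stake. An analyst who follows Statistical methods would not report the outcome in Table 3, and one who follows Table 3 would have to choose a model that the article does not name. Reduced readmission is also one of the stated HF hypotheses, so it should be settled before the data are seen which quantity tests it.

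**Working it through.** **What the plan's own power figure covers.** With 240 patients and 20% dropout, 192 remain, or 96 per arm. For a 0.4 SD difference at two-sided 0.05 (sidedness is not stated, so this is assumed), power is Φ(0.4 × √(96/2) − 1.96) = Φ(0.81) = 0.79, in line with the stated 80%. That figure concerns self-efficacy. No event rate, expected count or power is stated for readmissions.

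**Share of readmissions that a first-event model leaves out.** Let μ be the mean number of readmissions per patient in a window and k the dispersion (variance μ + kμ²). Both are assumed.

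- P(none) = exp(−μ) if k = 0, otherwise (1 + kμ)^(−1/k)
- Share that are repeats = 1 − (1 − P(none))/μ

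Example, μ = 0.4 and k = 1: P(none) = 1/1.4 = 0.714, so the share is 1 − 0.286/0.4 = 0.286.

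| μ | k = 0 | k = 0.5 | k = 1 | k = 2 |
|---|---|---|---|---|
| 0.15 | 0.071 | 0.102 | 0.130 | 0.180 |
| 0.25 | 0.115 | 0.160 | 0.200 | 0.266 |
| 0.4 | 0.176 | 0.236 | 0.286 | 0.363 |
| 0.6 | 0.248 | 0.320 | 0.375 | 0.457 |
| 0.9 | 0.341 | 0.417 | 0.474 | 0.553 |

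The mean grows with the length of the window, so the upper rows correspond to 30 days and the lower rows to longer windows.

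**Effect on estimate and power.** Inputs: 120 per arm ("The sample size goal is 240 patients (HF = 180, CRC = 60) equally divided between the intervention and control group"), no loss because readmissions come from hospital records, an assumed rate ratio of 0.7, and no allowance for deaths.

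- First-event hazard ratio, approximated by the ratio of cumulative hazards: HR = ln P(none | 0.7μ) / ln P(none | μ)
- Cox power = Φ(|ln HR| × √D/2 − 1.96), where D is the number of first events
- Count-model power = Φ(|ln 0.7|/SE − 1.96), where SE² = [(1/μ + k) + (1/(0.7μ) + k)]/120

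| μ (k = 1) | D | HR | Cox power | Count-model power |
|---|---|---|---|---|
| 0.25 | 42 | 0.723 | 0.182 | 0.207 |
| 0.4 | 61 | 0.734 | 0.225 | 0.279 |
| 0.6 | 80 | 0.746 | 0.259 | 0.355 |
| 0.9 | 103 | 0.761 | 0.283 | 0.437 |

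For μ from 0.25 to 0.9 and k = 0, 1 or 2, the gap runs from about 1 point (μ = 0.25, k = 0: 0.226 against 0.240) to about 15 points (μ = 0.9, k = 1). With k = 0 the hazard ratio equals the rate ratio of 0.70. With k above 0 it lies nearer to 1.

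The 6-month window applies to HF patients only, 90 per arm. At μ = 0.9 and k = 1:

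- Count model: SE = √(4.698/90) = 0.228, so power is Φ(0.357/0.228 − 1.96) = 0.35.
- Cox: D = 90 × (0.474 + 0.387) = 77, so power is Φ(0.273 × √77/2 − 1.96) = 0.22.

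**The case against.** The strongest reply is that the mismatch is one of wording. Statistical methods never says first readmission, and recurrent-event Cox models do use repeat events. No section says per patient, and the aim's reference to rates could mean the proportion readmitted. Time to first readmission by Cox is also a legitimate analysis. This has force: it is not established that repeat readmissions will be dropped, only that the method as named would drop them. It does not remove the point, because none of the definitions describes a time to first event and no extension is named.

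It is also fair that the size rests on assumed rates, that few repeats are expected within 30 days, and that days alive and out of hospital captures cumulative disease-related hospital time to six months.

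A reader might infer three stronger criticisms, which the article does not support:

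- **Waning.** Since "The intervention duration is six weeks following hospital discharge", a hazard ratio to 90 days or 6 months would average on- and off-intervention time. A count model does the same. Suppose a true ratio of 0.7 for 42 days and 1.0 afterwards. With a constant underlying rate, the count ratio is (42 × 0.7 + 48)/90 = 0.86 at 90 days and (42 × 0.7 + 138)/180 = 0.93 at 6 months. The corresponding Cox values are about 0.85 and 0.91, taking 50% readmitted by 6 months. This is no reason to prefer either model.
- **One pooled baseline hazard for HF and colorectal cancer.** This would be read from silence in one clause of a condensed article. Stratification may well stand in the analysis plan.
- **Death treated as simple censoring.** This is also inferred from silence, and a count model with a days-at-risk offset likewise ends exposure at death.

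**Conclusion.** The inconsistency stands. Every definition gives a count in fixed windows, while the single named analysis, taken in its ordinary meaning, estimates a hazard ratio for the first readmission. As written, it neither estimates the stated outcome nor uses repeat readmissions.

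The size cannot be fixed from the article. Under the means and dispersions assumed above, roughly 7% to 55% of readmissions would be unused, increasing with window length and with clustering within patients. The power cost is modest, about 1 to 15 percentage points with 120 per arm and a rate ratio of 0.7, and power is limited under either model. The point concerns secondary outcomes only and leaves the self-efficacy analysis and the sample size of 240 untouched.

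**What to change.** Preferred: in Statistical methods, replace the Cox clause with a statement that the number of readmissions in each window will be compared by negative binomial regression with log days at risk as offset, or by a recurrent-event rate model with robust variance. Adjust for the randomisation strata (diagnosis and site; site alone in the HF sub-study). Keep Cox regression as a supportive analysis of time to first readmission.

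Alternative: if first readmission is what is meant, keep Cox and redefine the outcome as time to first readmission in both Table 3 entries, in Secondary outcome measures and in HF sub-study outcome measures. Align the wording of the secondary aim as well.

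The preferred route costs one sentence and one additional model, and uses hospital records that the trial will collect anyway. The choice should be made before outcome data are seen by arm.
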